| **Drug Administration Plan** | The dosing phase of this study includes three stages: the single-dose phase, the multiple-dose phase, and the extended dosing phase. The pharmacokinetics of the single-dose and multiple-dose administrations are combined, during which safety, tolerability, and preliminary efficacy are observed.  **1. Single-Dose Phase**  The single-dose escalation phase will begin with the starting dose and proceed in an ascending order from low to high doses, with 3 to 6 subjects enrolled in each dose group. In each dose group, 3 subjects will be enrolled sequentially, and a single dose will be administered on Day 1 (D1) at that dose, followed by a 6-day observation period (D2-D7). Each subject will receive treatment with a single dose.  **2. Multiple-Dose Phase**  After completing the pharmacokinetic blood sampling for the single-dose administration, if the subject is well-tolerated, they will enter the multiple-dose phase, with doses administered on Days 8, 11, and 15. Each subject will receive the same dose as in the single-dose phase, with the dose-limiting toxicity (DLT) observation period defined as the first administration to 25 days after the first dose. Initially, only one subject will be enrolled in each dose group to observe their tolerability and safety within the 25 days following the first dose. Only if this subject does not experience a DLT will the remaining two subjects in the same dose group be allowed to enroll simultaneously.  If none of the 3 subjects in a dose group experience DLT, the trial will proceed to the next dose group. If 1 out of the 3 subjects in a dose group experiences DLT, an additional 3 subjects will be recruited to receive the same dose of the investigational drug, and they will be monitored for DLT occurrence.  If 1 DLT occurs among the 6 subjects, the trial will proceed to the next dose group. If 2 or more DLTs occur among the 3 subjects, or if 2 or more DLTs occur among the 6 subjects, the trial will be reduced to the previous dose group. If the previous dose group has fewer than 6 evaluable subjects, an additional 3 subjects will be enrolled to bring the total number of evaluable subjects to 6. If no more than 1 DLT occurs among the 6 evaluable subjects, the trial will be halted, and that dose group will be declared as the maximum tolerated dose (MTD). If the previous dose group has already reached 6 evaluable subjects, the trial will be halted, and that dose will be declared as the MTD.  During the multiple-dose escalation trial, real-time analysis of the pharmacokinetic (PK) data for the selected dose groups will be conducted to determine whether the drug reaches a saturation state in the body based on PK and pharmacodynamic (PD) indicators.  **3. Extended Treatment Phase**  After completing the single-dose and multiple-dose phases, if the efficacy assessment indicates clinical benefit for the subject, they will enter the extended dosing phase. In the extended dosing phase, treatment may continue according to the original dosing regimen or with adjustments to the dose based on the subject's tolerability and existing clinical results. Each dosing cycle lasts 21 days, with doses administered on Days 1, 4, 8, and 11 of each cycle. The number of extended dosing cycles will vary based on the patient's efficacy; subjects who achieve an objective response rate of partial response (PR) or higher after 6 cycles may continue receiving the treatment until disease progression, while those who do not reach PR will discontinue the treatment. Efficacy and safety data will continue to be collected during the extended dosing phase. |

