| Urine routine^d^ | **√** |  | **√** | **√** |  | **√** | **√** | **√** | **√**^#^ | **√** | **√** | **√** |
| Blood biochemistry^e^ | **√** |  | **√** | **√** |  | **√** | **√** | **√** | **√**^#^ | **√** | **√** | **√** |
| Coagulation^f^ | **√** |  | **√** | **√** |  | **√** | **√** | **√** | **√**^#^ | **√** | **√** | **√** |
| M protein^L^ | **√** |  |  |  |  |  |  | **√** | **√**（pre-administration）^m^ |  |  |  |
| Virological examination^g^ | **√** |  |  |  |  |  |  |  |  |  |  |  |
| 12-lead ECG ^h^ | **√** | **√**（Checked once before administration, and 2 hours, 6 hours after administration, as well as on D2 and D7） | | | √（Checked once 2 hours and 6 hours after administration on D8, and once before administration, as well as 2 hours and 6 hours after administration on D11 and D15, and once on D25） | | | | √（Checked once before administration on D1, D11, and D21, and once 2 hours after administration, with additional checks as deemed necessary by the investigator） | | | **√** |
| Radiographic examination^i^ | **√** |  |  |  |  |  |  | **√** |  |  | **√** | **√** |
| Bone marrow examination^n^ | **√** |  |  |  |  |  |  | **√** |  |  | **√** | **√** |
| Echocardiography^j^ | **√** | △ | △ | △ |  | △ | △ | △ | △ | △ | △ | △ |
| Efficacy evaluation^k^ |  |  |  |  |  |  |  | **√** |  |  | **√** | **√** |
| Compliance evaluation |  | **√** |  |  |  |  |  | **√** |  |  | **√** | **√** |
| Adverse events | **√** | **√** | **√** | **√** | **√** | **√** | **√** | **√** | **√** | **√** | **√** | **√** |
| Concomitant medication | **√** | **√** | **√** | **√** | **√** | **√** | **√** | **√** | **√** | **√** | **√** | **√** |

Note: **√** indicates mandatory items, and **△** indicates optional items based on specific circumstances.

The single-dose phase is from D1 to D7, and the multiple-dose phase is from D8 to D25. The DLT observation period is from D1 to D25. If the participant tolerates the treatment well, they may enter the continuation dosing phase on D26.

**BSA Calculation Formula: Dubois-Dubois formulas，BSA = (W ^0.425^ x H ^0.725^) x 0.007184，Weight (kg), Height (cm); The single and multiple doses are calculated based on the weight at the time of the first administration. In the continuation dosing phase, weight is measured again before each cycle. If the weight changes by 10% or more compared to the initial dosing weight, the dosage for that visit will be based on the actual weight. However, the dosage remains unchanged for each cycle.**

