The starting dose will be 1.2 mg/m², and dose escalation will be conducted according to the Modified Fibonacci Scheme, with escalation increments of 100%, 67%, 50%, 40%, 33%, and 33%. Only after completing the single and multiple administration phases of the previous dose group, and based on the tolerability and pharmacokinetic results of that dose group, can a decision be made on whether to proceed to the next dose group, until the maximum tolerated dose (MTD) is established. It is anticipated that the MTD will be determined within seven dose groups, with a maximum sample size projected to be 42 participants.

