Considering the information from preclinical studies and the administration methods of similar HDAC inhibitors in clinical settings (for example, Panobinostat is administered in cycles of 21 days, with four doses given in the first two weeks, where the interval between each pair of doses is no less than 3 days), the current dosing frequency for Purinostat Mesylate is provisionally set to a single administration and continuous dosing on days D1, D8, D11, and D15, with a 10-day interval. Subjects meeting the criteria as assessed by the physician will enter the continuation dosing phase, which consists of administering the drug on days 1, 4, 8, and 11 of each cycle, again with a 10-day interval, for a total cycle length of 21 days. The subsequent dosing frequency may be further adjusted based on the pharmacokinetic and pharmacodynamic results from the first subject.

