### Escalation Process

The trial begins with a low dose, enrolling 3-6 subjects in each dose group. The decision to proceed to the next dose group will be based on whether at least 3 evaluable subjects from the previous dose group experience Dose Limiting Toxicity (DLT) and the corresponding safety data within 25 days after the first administration. An evaluable subject is defined as one who has received ≥80% of the planned dose or has experienced DLT after at least one dose

The specific regulations for dose escalation are as follows:

Table 8 Dose Escalation Rules

| **Occurrence of DLT** | **Actions** |
| --- | --- |
| No DLT observed | Proceed to the next dose group |
| 1 DLT observed among 3 subjects | Recruit an additional 3 subjects to receive the same dose of the investigational drug and observe for DLT |
| 1 DLT observed among 6 subjects | Proceed to the next dose group |
| ≥2 DLTs observed among 3 or 6 subjects | Reduce to the previous dose group.   - If there are fewer than 6 evaluable subjects in the previous dose group, recruit an additional 3 subjects to reach a total of 6 evaluable subjects. If no more than 1 DLT is observed among the 6 evaluable subjects, terminate the trial, and that dose group will be considered the MTD. - If there are already 6 evaluable subjects in the previous dose group, terminate the trial, and that dose will be considered the MTD. |

**Enrollment Sequence for Subjects in the Same Dose Group:** At the beginning of each dose group, only 1 subject will be enrolled to observe the tolerability and safety of that subject within 25 days after the first administration.

- Only if this subject does not experience DLT can the remaining 2 subjects in the same dose group be enrolled simultaneously.
- If this subject experiences DLT, enrollment of the third subject can only occur after the second subject has completed the 25-day observation period following the first administration, and only if the second subject has not experienced DLT.

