## Definition of MTD

Within 25 days after the first dose, if ≤ 1 DLT occurs among 6 subjects, the highest dose that meets this criterion will be defined as the MTD. If all dose groups specified in the protocol have been completed and no DLT occurs in the highest dose group, then the highest dose will be determined as the MTD.

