## Subject Supplementation

Subjects who discontinue the study within 25 days after the first dose for reasons other than dose-limiting toxicities (DLTs) — such as participant withdrawal from the clinical trial, serious protocol violations, failure to meet inclusion/exclusion criteria, poor compliance, or early evidence of disease progression — may be supplemented to ensure that the number of evaluations for DLTs remains sufficient.

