**DLT Analysis Set**

The DLT analysis set includes participants who received at least 80% of the planned dosage within 21 days after the first dose, or who experienced a DLT after receiving at least one dose. This analysis set will be used for the analysis and summary of DLT events.

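### Neither definition of a DLT-evaluable subject requires observation to D25, and the two definitions differ, so the cohort denominator is not guaranteed to match the 25-day DLT window

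*Protocol*

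**What the plan says.** The 25-day window is fixed in several places. The notes to the general flowchart state: "The DLT observation period is from D1 to D25". Section 3.4 counts drug-related toxicities over 25 days from the first dose, and Section 3.5 opens the MTD rule with "Within 25 days after the first dose, if ≤ 1 DLT occurs among 6 subjects".

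Who counts towards that rule is defined twice.
- Section 3.2.4: "An evaluable subject is defined as one who has received ≥80% of the planned dose or has experienced DLT after at least one dose". It sets no time limit on dosing and no minimum follow-up.
- Section 10.1, DLT Analysis Set: "participants who received at least 80% of the planned dosage within 21 days after the first dose, or who experienced a DLT". It sets a 21-day limit and no minimum follow-up.

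For subjects who leave the study within 25 days for reasons other than a DLT, Section 4.7 says that they "may be supplemented to ensure that the number of evaluations for DLTs remains sufficient".

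On dosing, Section 3.2.2 sets "continuous dosing on days D1, D8, D11, and D15, with a 10-day interval". For the multiple-dose phase the synopsis adds: "Each subject will receive the same dose as in the single-dose phase". The DLT window therefore holds four equal planned infusions, the last on D15.

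**The concern.** The MTD is a primary objective and is meant to inform Phase II dosing. It is read from counts such as 0 of 3 or 1 of 6, so one wrongly classified subject can change a decision.

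The dose criterion can be met on D15, with D16-D25 still to come. After D15 the next scheduled laboratory tests, physical examination, vital signs and ECG are on D25. A subject who leaves on D16 misses that visit, apart from whatever is done at withdrawal. Some DLTs also need time to qualify: Section 3.4 requires at least 5 days for Grade 4 neutropenia without fever and at least 7 days for the Grade 4 thrombocytopenia criterion. If either begins after D15, it cannot be confirmed in someone who leaves on D16. Such departures are foreseeable, since Section 4.7 itself lists early progression and withdrawal.

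The 80% criterion can err the other way. A subject with a DLT is kept after a single dose, whereas a DLT-free subject must pass the dose test. Selection into the denominator then depends on the outcome.

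**Working it through.** **Plan's own figure.** Seven groups of 3 to 6 give 7 × 3 = 21 and 7 × 6 = 42, which reproduces the planned enrolment of 21-42. That range is exactly full cohorts, with nothing added for replacements.

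**Dose threshold.** With four equal infusions, 3/4 = 75% < 80% and 4/4 = 100%. Counted in whole infusions, the threshold means all four. Counted in mg, 0.80 × 4 = 3.2 dose-equivalents, so three full infusions plus 20% of the fourth would pass. The protocol does not say which basis applies. On either basis, a wholly omitted infusion leaves 75%.

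**Unobserved time.** A subject who leaves after D15 has been seen for 15 of 25 days; D16-D25 is 10/25 = 40% of the window.

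**Early leavers.** Assume a true 25-day risk p = 0.33. Under uniform onset, 40% of DLTs arise after D15, so the risk seen in a leaver is 0.6 × 0.33 = 0.198.
- No leaver: P(0/3) = 0.67³ = 0.30.
- One leaver: P(0/3) = 0.67² × (1 − 0.198) = 0.4489 × 0.802 = 0.36.
- Range for one leaver: if 20% of DLTs are late, 0.4489 × (1 − 0.264) = 0.33; if 60%, 0.4489 × (1 − 0.132) = 0.39.
- Extreme, all three leave unreplaced: 0.802³ = 0.52.

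The probability of escalating under the full 3+3 rule is (1−p)³ + 3p(1−p)² × (1−p)³. At p = 0.33 this is 0.301 + 0.444 × 0.301 = 0.434. With one leaver in each set of three it becomes 0.477, 0.520 or 0.562 for late shares of 20%, 40% or 60%.

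**Subjects with an omitted dose.** Let m be the assumed share of DLT-free subjects who miss a dose. The rate among those counted is p / [p + (1−p)(1−m)]. At p = 0.20:

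| m | Rate among counted subjects | 3+3 escalation probability |
|---|---|---|
| 0 | 0.200 | 0.709 |
| 10% | 0.217 | 0.671 |
| 20% | 0.238 | 0.626 |
| 30% | 0.263 | 0.572 |

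For example, at m = 10%: 0.2 / (0.2 + 0.8 × 0.9) = 0.2 / 0.92 = 0.217.

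**Does another rule catch the omitted dose?** Section 3.4 makes an interruption of more than 14 days for unresolved toxicity a DLT. If the D15 dose is withheld, D25 comes 10 days after D15 and 14 days after the D11 dose. Neither exceeds 14, so this criterion is not met within the window.

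**The case against.** Follow-up to D25 is addressed elsewhere for live escalation. Section 3.1 opens the next group "Only after completing the single and multiple administration phases of the previous dose group", and the multiple-dose phase ends on D25. Section 3.2.4 bases the decision on DLTs and safety data over 25 days, and the first subject of each group is watched for 25 days before the next two enrol. The purpose stated in Section 4.7 implies that someone who leaves early is not a full evaluation. Section 4.6 asks for a complete final assessment at withdrawal. All of this stands and reduces the practical risk. What it does not do is make D25 follow-up a condition of an individual's evaluability, require replacement, or take the early leaver out of the Section 10.1 set.

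A reader might infer four stronger points that the documents do not support.
- That DLTs on D22-D25 are lost because Section 10.1 says 21 days. In that sentence the 21 days limit when dosage is received. The DLT limb is separate, and a DLT keeps its 25-day definition.
- That the threshold certainly means all four infusions. This holds only if whole infusions are counted.
- That the toxicity of a dropped subject is discarded. The subject stays in the Safety Set, and Section 10.4 reports the adverse events by dose group. Only the DLT denominator changes.
- That the cohort denominators are wrong. If every subject receives four doses and reaches D25, they are right.

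Whether a subject with a dose omitted for toxicity should count is a design choice, not an error with one correct answer. The present rule raises the observed rate and so makes escalation less likely.

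**Conclusion.** The point holds as a defect of definition. Two sections define the denominator for the primary objective differently, and neither guarantees that a DLT-free subject was observed over the 25 days that the MTD rule uses. The consequences run in opposite directions: early leavers counted as DLT-free lower the observed rate, and excluding DLT-free subjects with an omitted dose raises it.

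The 75% figure and the lack of a follow-up condition come directly from the text. The sizes do not: DLT risk, timing of onset and missed-dose share are all assumptions, since the protocol gives none. The fair single-subject illustration is a move in the chance of 0/3 from 30% to 36% (33% to 39% across the late shares shown). The 52% case should not be used as a headline, because it needs all three subjects to leave straight after the last dose, none to be replaced, and escalation to proceed despite Sections 3.1 and 3.2.4.

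**What to change.** 1. Use one definition, worded identically, in Sections 3.2.4 and 10.1. Evaluable means either a DLT at any time in D1-D25, or the minimum dosing **and** DLT assessment completed through D25.
2. State the minimum dosing as a number of the four infusions or as a percentage of total planned mg.
3. In Section 4.7, state that subjects who are not evaluable under this definition will be replaced and are not in the DLT set. At present that section covers only subjects who leave the study, not those who stay with too few doses.
4. Reconcile the 21-day dosing limit in Section 10.1 with Section 3.2.4, which has none. Simply changing 21 to 25 is not enough: without the follow-up condition, a dose given at the end of the window would count with no observation after it.
5. State whether a DLT-free subject with a dose omitted for drug-related toxicity, but followed to D25, is counted.

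The cost is wording in three sections and an occasional extra replacement subject, for which the 21-42 range leaves no explicit allowance.

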## Statistical Methods

The statistical analysis of this study will be conducted using the SAS 9.4 statistical software (or a later version). The results will be reported in summary tables (or graphs) and listings, primarily utilizing descriptive statistical methods for summarization. Numerical variables will be described using the mean, standard deviation (SD), median, first quartile (Q1), third quartile (Q3), minimum (Min), and maximum (Max). Categorical variables will be described using counts and percentages for each category.

## Baseline Characteristics of Participants

Demographic information for all participants during the screening period will be provided, including data on age, sex, medical history, treatment history, histopathology, lesion characteristics, and screening eligibility criteria. This baseline information will be summarized and categorized by dose group.

## Tolerability/Safety Analysis

In the safety analysis, adverse events/adverse reactions will be summarized by dose group using qualitative descriptions of the number of occurrences and incidence rates after medical coding is completed. A listing will be provided that includes information on the names of adverse events/adverse reactions, standard names, system classifications, occurrence times, severity, relationship to the investigational drug, whether they are serious adverse events, and outcomes.

Clinical significance of laboratory tests, results of physical examinations, and electrocardiogram (ECG) results will be analyzed using cross-tabulations for changes at each visit stage relative to pre-treatment values. A listing will also be provided for results that were normal/clinically insignificant prior to treatment but became abnormal/clinically significant afterward.

Key laboratory parameters, vital signs, ECOG scores, 12-lead ECGs, and cardiac enzyme profiles will be summarized quantitatively for the values at each visit, and line graphs will be created for the key parameters.

A summary of DLT events for each dose will also be provided.

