## Inclusion Criteria

1. Age between 18 and 70 years, regardless of gender.
2. Diagnosis confirmed by histopathological or cytological examination (according to the "Diagnostic Criteria and Efficacy Standards for Hematological Diseases" (4th Edition) published by Science Press) for hematological malignancies, including but not limited to B-cell lymphoma, multiple myeloma, B-cell acute leukemia, T-cell lymphoma, and T-cell acute leukemia. Patients must have experienced disease progression, relapse, or be unsuitable for standard treatment after receiving standard treatment regimens (specific definitions for relapsed or refractory disease can be found in Section 4.2).
3. No severe organic lesions in the heart, lungs, liver, or kidneys (LVEF≥50%; total bilirubin ≤1.5×ULN; ALT ≤1.5×ULN; AST ≤1.5×ULN; serum creatinine ≤1.5×ULN or CCr > 40 mL/min).
4. No severe coagulation dysfunction (PT≤1.5×ULN, APTT≤1.5×ULN, TT≤1.5× ULN, and FIB≥1.0 g/L).
5. No severe hematological abnormalities (absolute neutrophil count≥1.5×10^9^/L, platelets≥75×10^9^/L, hemoglobin≥80 g/L), and no transfusion of platelets, red blood cells, or hemoglobin within the 2 weeks prior to screening.
6. At least 4 weeks or more than 5 half-lives since the last anti-tumor treatment (chemotherapy, radiotherapy, biological therapy, or immunotherapy) prior to enrollment.
7. Expected survival time of≥12 weeks.
8. ECOG performance status of≤2.
9. Willingness to participate in the study and sign the informed consent form.

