**Hematologic toxicity**

Hematological adverse reactions (thrombocytopenia, neutropenia, anemia) commonly occur during the early stages of treatment. Close monitoring of complete blood count (CBC) is essential, and adjustments to medication and management of related side effects should be made based on the results, ensuring safety while striving to maintain the same dosage.

For grade 1–3 neutropenia, the treatment regimen should not be changed temporarily, and granulocyte colony-stimulating factor (G-CSF) should be added. CBC should be conducted approximately every two days to monitor whether neutrophil counts recover. If there is no recovery, consideration may be given to adjusting the treatment plan. If grade 4 neutropenia persists for≥5 days, despite the addition of G-CSF, Purinostat Mesylate treatment should be permanently discontinued unless the investigator and sponsor agree to continue treatment at a reduced dose in the best interest of the subject.

Patients with multiple myeloma often present with thrombocytopenia and anemia. Close monitoring of platelet counts is essential. For grade 1–3 thrombocytopenia, it is recommended to maintain the dose under supportive treatment with recombinant human thrombopoietin injection (e.g., TPO), recombinant human interleukin-11, or platelet transfusions to prevent life-threatening or severe gastrointestinal or pulmonary bleeding. If bleeding occurs, treatment should be immediately suspended until platelet counts return to baseline levels. If the patient experiences severe anemia (e.g., hemoglobin<60 g/L), red blood cell transfusions or erythropoietin injections may be used to increase red blood cell counts.

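### The laboratory and ECG shift outputs run on clinical significance, so a result already rated significant at entry can worsen with no shift and no listing, and no stated table shows worsening by CTCAE grade and dose group

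*Protocol*

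**What the plan says.** Section 10.4 sets the unit of the shift analysis: "Clinical significance of laboratory tests, results of physical examinations, and electrocardiogram (ECG) results will be analyzed using cross-tabulations for changes at each visit stage". The comparator is the result before dosing. It then fixes what is listed: "A listing will also be provided for results that were normal/clinically insignificant prior to treatment but became abnormal/clinically significant afterward". It gives no definition of clinical significance.

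The same section plans four other safety outputs:

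- adverse events by dose group, as number of occurrences and incidence;
- an adverse event listing that includes "occurrence times, severity, relationship to the investigational drug, whether they are serious adverse events, and outcomes";
- key laboratory parameters and ECGs, which "will be summarized quantitatively for the values at each visit, and line graphs will be created for the key parameters";
- a DLT summary for each dose.

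Section 10.2 includes the first quartile and the minimum among the descriptive statistics.

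On who may enter, inclusion criterion 5 (section 4.4) requires neutrophils of at least 1.5×10^9/L and "platelets≥75×10^9^/L, hemoglobin≥80 g/L". Section 8.4 says of one of the named diseases: "Patients with multiple myeloma often present with thrombocytopenia and anemia".

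**The concern.** A shift table is meant to show, subject by subject, how far a value moved from where it started. If its categories are only normal, clinically insignificant and clinically significant, the last has no further step. A subject who starts there can go to a life-threatening value and still be tabulated as unchanged, and the listing rule excludes the same subject.

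In this population that is a realistic starting point for at least one blood count. Cytopenia is also the first risk that section 8.4 addresses, and that section describes it as common early in treatment. At stake is whether a reader of the tables can see, by dose group, who worsened to a severe grade.

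**Working it through.** No sample size, error rate or event count bears on this, so the check sets the stated rules side by side. The three-level rating below is read from the wording of the listing rule; section 10.4 does not spell out the levels.

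**Step 1. Paths of worsening under section 10.4**

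| Rating at entry | Rating afterwards | Shift shown? | In the listing? |
| --- | --- | --- | --- |
| Normal | Clinically significant | Yes | Yes |
| Abnormal, insignificant | Clinically significant | Yes | Yes |
| Abnormal, insignificant | Still rated insignificant | No | No |
| Clinically significant | Clinically significant, worse grade | No | No |

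The last row is the one that matters. An abnormal entry value does not by itself put a subject there; it must have been rated significant.

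**Step 2. Which parameters can start in the last row**

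Entry limits (section 4.4) against the Grade 1 limits in Appendix 14.3:

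- Haemoglobin: entry from 80 g/L; Grade 1 ends at 100 g/L. Values of 80 to 99 g/L are eligible and worse than Grade 1, so a rating of clinically significant is plausible.
- Platelets: entry from 75×10^9/L; Grade 1 ends at 75×10^9/L. At most Grade 1 at entry.
- Neutrophils: entry from 1.5×10^9/L; Grade 1 ends at 1.5×10^9/L. At most Grade 1 at entry.
- QTc: section 4.5 excludes above 450 ms in men and above 480 ms in women. A woman between 450 and 480 ms is eligible, and how that tracing is rated is left to the investigator.

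Example: platelets of 80 at entry that fall to 10×10^9/L show no shift only if 80 was rated clinically significant. If it was rated insignificant, the fall is both tabulated and listed.

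**Step 3. Do the other planned outputs show grade-level worsening by dose group?**

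- Adverse event summary: by dose group, but only counts and incidence. Section 7.1 names severity as an evaluation indicator, yet in 10.4 severity appears only in the listing.
- Adverse event listing: has severity, one line per event, not tabulated.
- Per-visit summaries: a platelet value of 10 at a scheduled visit would appear as the minimum, but the minimum is not linked to that subject's baseline.
- DLT summary: covers a subset (section 3.4). Grade 3 thrombocytopenia counts only with bleeding of WHO Grade 2 or more; Grade 4 only if it lasts at least 7 days with at least 2 transfusions, acute leukaemia excluded; afebrile Grade 4 neutropenia only if it lasts at least 5 days. The general haematologic list has no anaemia item, and the window closes at 25 days while extension cycles continue.

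**Step 4. Visit-based tabulation**

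Scheduled counts in the first two dosing phases fall on D2, D7, D11, D15 and D25 (sections 6.2 and 6.3), which leaves 25 − 15 = 10 days between the last two. Section 8.4 foresees counts about every two days during neutropenia. A table "using cross-tabulations for changes at each visit stage relative to pre-treatment values" has no stated place for those extra values.

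**Step 5. Size**

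The share of worsening absent from the shift table and its listing depends on how many subjects are rated clinically significant at entry. The protocol gives no figure, so the share can run from none upward and cannot be narrowed. What can be computed is the weight of one subject in a group of 3 to 6 (section 3.2.3): 1/6 = 17% to 1/3 = 33%.

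**The case against.** The strongest reply is that worsening from an abnormal baseline is already captured. Section 8.1.1 counts abnormal laboratory findings and worsening of pre-existing conditions as adverse events, section 8.1.2 requires every one to be graded by CTCAE v5.0, and section 10.4 lists them with severity. Per-visit minima and line graphs show falling counts. All of this stands: no event disappears from the trial's safety record.

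The second reply is that worst-grade shift tables and the handling of unscheduled values are ordinary content of a statistical analysis plan, to which section 10.8 defers detail. That would dispose of the point if section 10.4 were silent. It is not: it states the categories and the listing trigger, and those are what need changing.

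Three stronger readings are tempting, and the protocol does not support them.

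- A reader might infer that everyone with an abnormal count at entry is missed. The trigger includes clinically insignificant baselines, so only those already rated significant are affected.
- A reader might infer that a large share of Grade 3 to 4 worsening goes unseen. Any such percentage would only restate an assumed fraction of significant baselines, and it would apply to one table and one listing, not to all safety reporting.
- A reader might infer that the Phase II dose is biased toward looking safe. Escalation and the MTD rest on DLT counts (sections 3.2.4 and 3.5), whose haematologic criteria use grades, durations and clinical conditions. The shift table drives none of that.

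**Conclusion.** The point holds in a limited form. As section 10.4 is written, a result already rated clinically significant at entry can worsen without a shift and without entering the shift listing. This is most likely for haemoglobin of 80 to 99 g/L. For platelets, neutrophils and QTc it depends on how the investigator rated the entry value. The events remain visible as graded, listed adverse events, in per-visit minima and, where they qualify, as DLTs; MTD selection is unaffected.

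What is lacking is any stated table of grade-level worsening by dose group. The conclusion assumes that the rating levels are those implied by the listing rule and that at least some entry values are rated significant; the protocol does not say how many. Severity is minor: a reporting improvement, not a flaw that hides harm.

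**What to change.** Amend section 10.4 as follows.

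1. For laboratory parameters and QTc that CTCAE v5.0 grades, replace the clinical-significance cross-tabulation by a table of baseline grade against worst post-baseline grade, using scheduled and unscheduled values, by dose group, once for D1 to D25 and once for the whole treatment period.
2. List every subject who worsens by at least one grade to Grade 3 or higher, whatever the baseline.
3. Summarise adverse events by maximum CTCAE grade and dose group.

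The clinical-significance tabulation can stay for physical examination and for findings that CTCAE does not grade. The grading system and the values are already in the trial, so the cost is a few sentences, revised table shells and programming. No dose, DLT rule or other clinical rule changes.
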